### Randomization and blinding

Randomization of dashboard onset timing will be performed using a computer-generated random number sequence, consistent with recommendations for randomized SCEDs (27, 28). Allocation will be concealed using sequentially numbered, opaque, sealed envelopes prepared by a statistician not involved in recruitment. Patients will be stratified by primary diagnosis (stroke vs. non-stroke) and baseline functional level [dependent [FIM motor score ≤58] vs. independent [FIM motor score >58]] to ensure balanced representation across onset strata. Neither patients nor clinical staff can be blinded to dashboard activation, as the intervention involves an active visual feedback display. However, the primary outcome (daily active time) is measured objectively and continuously by the PreSAGE system, eliminating observer bias in outcome ascertainment. The statistician conducting the primary analysis will be blinded to onset stratum assignments.

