### Phase 3: randomized multiple baseline evaluation (months 13–24)

#### Study design

The primary quantitative evaluation employs a randomized multiple baseline design across participants (28, 29, 32), in which each patient undergoes two phases during their admission:
**Phase A (Baseline Observation):** From admission, the PreSAGE system continuously monitors patient activity. Activity data are collected and processed but no feedback is provided to the patient or treating team. This observation-only period provides individualized baseline data for each patient, lasting 3 to 7 days depending on the randomly assigned onset point (see Randomization below), consistent with the A phase in SCED methodology (27, 31).**Phase B (Dashboard Intervention):** At the randomly assigned onset point, the patient-facing dashboard is activated on a bedside tablet and the clinician-facing dashboard becomes available to the treating team. Therapists set personalized activity goals, and patients receive continuous feedback on their progress. Thermographic monitoring continues throughout.The critical design feature is the randomized timing of the A-to-B transition. Each patient will be randomly assigned, using a computer-generated allocation sequence with concealed envelopes, to one of five onset points: post-admission day 3, 4, 5, 6, or 7. If the assigned onset day falls on a weekend, activation will be deferred to the next weekday to ensure research assistant availability and clinical team presence for goal-setting. This ensures that each patient has a minimum baseline observation period of 72 h (to establish a stable pre-intervention trend) while staggering the transition point across the sample in a manner consistent with the MBD framework (29, 32). Ten patients will be assigned to each of the five onset strata, yielding 50 patients total.

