### Data analysis

#### Quantitative analysis

The primary analysis will use a piecewise multilevel growth model (42, 45) to estimate the within-person effect of dashboard activation on daily active time. This analytic approach is well-established for combining data from multiple SCEDs into a unified multilevel framework (42). The two-level model (Level 1: daily observations nested within Level 2: patients) will take the form:
*Level 1: Y*ti* = β*0i* + β*1i*(Day*ti*) + β*2i*(Phase*ti*) + β*3i*(Day_post*ti*) + e*ti*Level 2: β*0i* = γ*00* + u*0i*; β*1i* = γ*10* + u*1i*; β*2i* = γ*20* + u*2i*; β*3i* = γ*30* + u*3iwhere Yti is the daily active time for patient *i* on day *t*; Dayti is the centered day variable; Phaseti is a binary indicator (0 = baseline, 1 = post-dashboard); Day_postti captures the post-activation trend (0 during baseline, days since activation during intervention); *β*2i captures the immediate level change (jump in activity at dashboard onset); *β*3i captures the change in slope (sustained trend change); and eti is the residual error modeled with an AR(1) structure to account for serial autocorrelation.

The Level 2 equations model between-patient variation in intercepts and slopes as random effects. Fixed effects (*γ*00, *γ*10, *γ*20, *γ*30) represent the average population-level baseline, pre-intervention trend, level change, and slope change. The primary hypothesis test is that *γ*20 (average immediate level change) and/or *γ*30 (average sustained slope change) differ significantly from zero.

Sensitivity analyses will include: (a) adjusting for patient-level covariates (age, diagnosis, baseline FIM, Clinical Frailty Scale score) in Level 2 equations; (b) testing different lag specifications (immediate vs. 1-day delayed effect); (c) modelling onset stratum as a fixed effect to test whether timing of activation moderates the intervention effect; (d) excluding patients with fewer than 14 days of total data (approximately 18% based on Phase 1 length of stay distribution); and (e) using Bayesian estimation as a robustness check. All analyses will follow the intention-to-treat principle based on assigned onset day.

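### The primary-analysis statistician cannot be blinded to onset stratum as written, because the primary model's own covariates show each patient's onset day

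*Protocol article*

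**What the plan says.** Under Randomization and blinding, the Protocol article accepts that neither patients nor clinical staff can be blinded to activation. It then makes one blinding claim: "The statistician conducting the primary analysis will be blinded to onset stratum assignments". It gives no time limit, masking method or unblinding point.

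The Phase 3 Study design section defines what is to be hidden. Each patient is randomised "to one of five onset points: post-admission day 3, 4, 5, 6, or 7", and "Ten patients will be assigned to each of the five onset strata, yielding 50 patients total". The stratum and the assigned onset day are therefore the same thing.

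The Quantitative analysis section sets out the primary model. Its Phase term "is a binary indicator (0 = baseline, 1 = post-dashboard" and its Day_post term "captures the post-activation trend (0 during baseline, days since activation during intervention". The same section adds: "All analyses will follow the intention-to-treat principle based on assigned onset day".

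**The concern.** The person named as blinded is the one conducting the primary analysis, and that analysis cannot be run without the information said to be withheld. In a parallel-group trial the arms can be called X and Y until the results are signed off. Here the exposure is a point in time within each patient's series, and the model has to know where it lies.

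What is at stake is what the trial can truthfully report. Patients and staff are unblinded, so analyst blinding is the only blinding claimed. If a decision affecting the estimate is still open when the model is fitted, it will be taken with the true onset in view, and the report will say it was not.

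**Working it through.** The plan attaches no figure to this claim, so there is none to reproduce. The question is whether the stratum can be read from the columns that the primary model requires.

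**Inputs (Protocol article)**
- Onset stratum = assigned onset day, 3 to 7, with 10 patients in each (Study design).
- Model columns: Day, Phase, Day_post (Quantitative analysis).
- All analyses use the assigned onset day (Quantitative analysis).
- If the assigned day falls on a weekend, activation moves to the next weekday (Study design).

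**Step 1: recover the onset day.** On any row with Phase = 1, Day_post = Day − onset day, so

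onset day = Day − Day_post.

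Example: a patient assigned to day 5 has Day_post = 7 on day 12, and 12 − 7 = 5. On day 6, Day_post = 1, and 6 − 1 = 5. One post-onset row is enough. Centring Day by a common constant shifts every answer equally and still sorts patients into the five strata in order.

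**Step 2: check it with missing days.** In 2,000 simulated patients (24 days each, onset day 3 to 7, and an assumed 10% of days missing at random), the rule recovered the onset day for 2,000 of 2,000.

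**Step 3: try recoding.** Renaming the strata, or swapping 0 and 1 in Phase, leaves the change point in the series. Dropping Day_post is not possible, because the model needs it, and the first row with Phase = 1 would still mark the onset.

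**Step 4: does weekend deferral hide the stratum?** Suppose the covariates were coded from actual activation, contrary to the assigned-day rule. All combinations of admission weekday and assigned day were listed, counting admission as day 0 and weighting them equally (both are assumptions):

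| Admissions | Combinations | Deferred | Assigned day not unique, given actual activation and admission weekday |
|---|---|---|---|
| All seven days | 7 × 5 = 35 | 10/35 = 28.6% | 13/35 = 37.1% |
| Weekdays only | 5 × 5 = 25 | 7/25 = 28.0% | 11/25 = 44.0% |

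This would blur the stratum label for some patients. The onset used in the model would still be visible for all of them.

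**Step 5: the exception.** A patient discharged before the onset day has no row with Phase = 1, so the stratum is not revealed. Such a patient has no post-onset data and so no before-and-after contrast.

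**Step 6: what is still open when the model is fitted?**
- Already fixed for the primary model: random effects on all four coefficients, AR(1) residuals, linear Day and Day_post terms, and an effect starting at activation (Quantitative analysis).
- Settled before Phase 3: which activity states count, by F1 ≥ 0.80 (Outcome measures), in a validation using samples from Phase 1 patients (Algorithm validation).
- Not fixed in the article: the rule for incomplete monitoring days (camera downtime is anticipated under Sample size justification) and what to do if the model does not converge.

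**The case against.** The best defence is that the sentence means blinding until the model and code are locked, and that masking mechanics belong in a full protocol or SAP that is not shown. Part of this stands: such blinding is feasible, and an article need not describe the mechanics. But the sentence covers the statistician conducting the analysis, not preparing it, and nothing in the article limits it in time. The problem is a positive statement that the article's own model contradicts, not a missing detail.

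Three stronger readings are tempting, and the document does not support them.

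- *No analyst blinding is possible in this design.* A reader might infer this from Step 3. It goes too far, because rules and code can be finalised on scrambled onset days. The claim cannot operate as written, but a workable form exists.
- *The unblinded analyst could move the estimate by a material part of the 18-minute target.* Nothing in the article supports a figure. The choices that would matter most (random effects, recovery shape, lag) are written into the primary model. A difference between alternative models would not in any case measure bias from an unblinded analyst.
- *The sensitivity analysis "modelling onset stratum as a fixed effect to test whether timing of activation moderates the intervention effect" proves the breach.* It does need the stratum, but the blinding claim is confined to the primary analysis, and this analysis could follow unblinding. The contradiction rests on Phase and Day_post alone.

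**Conclusion.** The point holds as a contradiction between the blinding statement and the primary model. The analyst can read the onset day for every patient with post-onset data, so the claimed blinding cannot operate while the primary analysis is being run.

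The consequence is moderate. Automated outcome capture limits ascertainment bias, and the form of the model is published. No estimate, alpha level, sample size or power figure changes. What remains is a small set of day-level and fallback decisions that the claimed blinding does not protect, and a report that would describe a safeguard that was not in force.

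The conclusion rests on reading the sentence literally and on covariates coded from the assigned onset day. Coding from actual activation would not change it. If the full protocol or SAP limits the blinding to the period before code lock, the article's sentence still needs that qualification.

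**What to change.** Replace the sentence with a statement of blinding up to code lock, along these lines: the analysis statistician will remain blinded to true onset days until the data-cleaning rules, day-level exclusions, convergence fallback and code for the primary and sensitivity analyses have been finalised, locked and dated; the locked code will then be applied to the true onset days.

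To make this workable:

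- The statistician who holds the allocation list supplies a dataset in which onset days are re-drawn or permuted across patients. This must be someone other than the analyst. The article says only that the envelopes are prepared by a statistician not involved in recruitment.
- The permutation is done within the randomisation cells (stroke or non-stroke, by FIM motor score ≤58 or >58). It must not be done within onset strata: everyone there has the same assigned day, so nothing would change.
- Fields that start only at activation, such as dashboard interaction counts and goals set, are withheld until lock because they also show the onset.
- The lock covers the sensitivity analyses as well as the primary model.

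If the team does not want this procedure, it should delete the claim and state that the analyst is not blinded.

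The cost is one scrambled dataset and a short wording change. The article anticipates Phase 3 from end 2026, so the change can be made before any patient is randomised.

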### Qualitative component: semi-structured interviews

A qualitative process evaluation will be conducted following Phase 3 data collection, consistent with the explanatory sequential design (34). The qualitative component follows the Medical Research Council framework for process evaluation of complex interventions (35) and will explore: (a) participant experiences with the monitoring system and dashboard, (b) perceived mechanisms of effect (or lack thereof), (c) barriers and facilitators to engagement, (d) privacy perceptions, and (e) contextual factors influencing implementation.

Purposive sampling will recruit participants representing diverse perspectives:
**Patients (*n*** **=** **10–15):** Sampled for maximum variation in age, diagnosis, functional level, and dashboard engagement level (high, moderate, and low users as defined by interaction frequency terciles). Interviews will be conducted within 48 h prior to planned discharge.**Ward sisters (*n*** **=** **2–3):** Senior nursing staff responsible for resource planning and dashboard-informed workflow decisions.**Clinicians (*n*** **=** **4–6):** Including therapists (physiotherapists and occupational therapists) and physicians involved in dashboard-informed goal setting and clinical decision-making.Topic guides will be developed based on the study objectives, piloted with two participants from each group, and iteratively refined. Interviews will be audio-recorded with consent, transcribed verbatim, and de-identified. Analysis will use reflexive thematic analysis (43) following Braun and Clarke's six-phase approach: familiarization with the data, generating initial codes, constructing themes, reviewing themes, defining and naming themes, and writing up. Two researchers will independently code 25% of transcripts; discrepancies will be resolved through discussion to enhance analytical rigor. Thematic saturation will be assessed using an information power framework (44), considering the study's specific aims, sample specificity, and theoretical positioning. NVivo (Lumivero) will be used for data management.

### Mixed-Methods integration

Integration of quantitative and qualitative findings will follow a joint display approach (37). A convergence matrix will be constructed to systematically compare quantitative activity trajectories with qualitative themes across key dimensions: engagement mechanisms, barriers to use, differential response patterns, and contextual influences. Specifically, qualitative themes will be mapped to quantitative subgroup analyses (e.g., whether patients who describe high motivation in interviews also demonstrate steeper post-onset activity increases, and whether patients who report usability barriers show lower dashboard interaction rates and smaller activity gains). The meta-inference will address: does the DREAMT intervention improve activity levels, for whom, through what mechanisms, and under what conditions (34, 36).

### Data analysis

#### Quantitative analysis

The primary analysis will use a piecewise multilevel growth model (42, 45) to estimate the within-person effect of dashboard activation on daily active time. This analytic approach is well-established for combining data from multiple SCEDs into a unified multilevel framework (42). The two-level model (Level 1: daily observations nested within Level 2: patients) will take the form:
*Level 1: Y*ti* = β*0i* + β*1i*(Day*ti*) + β*2i*(Phase*ti*) + β*3i*(Day_post*ti*) + e*ti*Level 2: β*0i* = γ*00* + u*0i*; β*1i* = γ*10* + u*1i*; β*2i* = γ*20* + u*2i*; β*3i* = γ*30* + u*3iwhere Yti is the daily active time for patient *i* on day *t*; Dayti is the centered day variable; Phaseti is a binary indicator (0 = baseline, 1 = post-dashboard); Day_postti captures the post-activation trend (0 during baseline, days since activation during intervention); *β*2i captures the immediate level change (jump in activity at dashboard onset); *β*3i captures the change in slope (sustained trend change); and eti is the residual error modeled with an AR(1) structure to account for serial autocorrelation.

The Level 2 equations model between-patient variation in intercepts and slopes as random effects. Fixed effects (*γ*00, *γ*10, *γ*20, *γ*30) represent the average population-level baseline, pre-intervention trend, level change, and slope change. The primary hypothesis test is that *γ*20 (average immediate level change) and/or *γ*30 (average sustained slope change) differ significantly from zero.

Sensitivity analyses will include: (a) adjusting for patient-level covariates (age, diagnosis, baseline FIM, Clinical Frailty Scale score) in Level 2 equations; (b) testing different lag specifications (immediate vs. 1-day delayed effect); (c) modelling onset stratum as a fixed effect to test whether timing of activation moderates the intervention effect; (d) excluding patients with fewer than 14 days of total data (approximately 18% based on Phase 1 length of stay distribution); and (e) using Bayesian estimation as a robustness check. All analyses will follow the intention-to-treat principle based on assigned onset day.

Secondary analyses for clinical outcomes (FIM, FAC, MBI, length of stay, discharge destination, complications) will use generalized linear models adjusted for baseline characteristics. Dashboard utilization patterns will be explored using descriptive statistics and latent class analysis to identify distinct engagement profiles. Subgroup analyses will compare intervention effects between functionally dependent and independent patients, with the hypothesis that dependent patients may show primary improvements in clinician-mediated outcomes (nursing engagement frequency, time to first sit-out, complication rates) while independent patients may show primary improvements in self-directed activity outcomes (daily active time, exercise compliance, dashboard utilization). The dose-response relationship between dashboard interaction frequency and activity changes will be examined using the interaction count as a time-varying covariate in the multilevel model.

All quantitative analyses will be conducted using R (R Foundation for Statistical Computing, Vienna, Austria) with the “lme4”, “nlme”, 'SingleCaseES', and “brms” packages.

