Additionally, Monte Carlo power simulations (2,000 replications) were conducted to evaluate the study's ability to detect intervention effects under the piecewise multilevel growth model. Data were generated assuming 50 participants (10 per onset stratum), a median of 24 daily observations each (based on Phase 1 empirical length of stay; IQR 15–35 days), a within-person residual standard deviation of 25 min, between-patient intercept standard deviation of 40 min, and within-person autocorrelation of 0.3. The study has greater than 80% power to detect an immediate level change of 10% in daily active time at dashboard onset (18 min; *α* = 0.05, two-sided), and greater than 99% power for a 15% level change (27 min, within-person d = 1.08). The study is primarily powered for the immediate level change parameter (*γ*₂₀); detection of the sustained slope change parameter (*γ*₃₀) would require larger per-day effects given the relatively short post-onset observation period. The sample of 50 provides adequate headroom for anticipated data attrition (early discharge, camera downtime) and planned subgroup analyses by functional level. We note that, while the sample is adequately powered for the primary immediate level-change parameter, the planned functional-level subgroup comparisons and the sustained slope-change parameter are powered to detect only larger effects given the shorter post-onset observation window; these analyses are therefore pre-specified as exploratory and hypothesis-generating rather than confirmatory.

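### The primary hypothesis test admits the slope change γ30 through an undefined and/or rule, while the sample-size section classes the same parameter as exploratory

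*Protocol article*

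**What the plan says.** Two sections of the Protocol article bear on this.

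- **Data analysis, Quantitative analysis.** The model has a baseline level (γ00), a baseline trend (γ10), a level change at activation (γ20) and a change in slope after activation (γ30). The primary hypothesis test concerns γ20 ("average immediate level change) and/or") γ30 ("average sustained slope change) differ significantly from zero"). No significance level per coefficient, joint test, order of testing or split of alpha is given there.
- **Sample size justification.** "The study is primarily powered for the immediate level change parameter", with power quoted at "0.05, two-sided". The section then says that the functional-level subgroup comparisons and "the sustained slope-change parameter are powered to detect only larger effects", and concludes that "these analyses are therefore pre-specified as exploratory and hypothesis-generating rather than confirmatory".

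**The concern.** A parameter cannot be both exploratory and sufficient by itself for the primary hypothesis. As published, the analysis section puts γ30 inside the primary test and the sample-size section takes it out. Whoever runs the analysis could cite either section, so which coefficient decides the trial could be settled after the results are known.

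The and/or wording also leaves the decision rule open. Read as two separate tests with success on either, it gives two chances at a false positive where the sample-size section budgets for one. The second chance rests on the parameter that the plan itself describes as less well powered. The Limitations section adds that three-day baselines may give less stable estimates, and the slope change is measured against exactly that baseline trend.

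**Working it through.** **1. Inputs.**

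From Sample size justification: "50 participants (10 per onset stratum"), residual SD 25 min, between-patient intercept SD 40 min, autocorrelation 0.3, median 24 daily observations (IQR 15–35). The same section also mentions 21 daily points. From Study design: activation at "one of five onset points: post-admission day 3, 4, 5, 6, or 7".

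Not given, so assumed: random-effect SDs of 0–3 (Day), 0–25 (Phase) and 0–3 (Day_post). Length of stay was fixed at 24 days, fixed at 21 days, or log-normal with median 24 and IQR 15–35. Day_post was counted as zero on the first intervention day. Counting it from one lowers the correlation in step 3 and moves the error slightly closer to the independence figure.

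**2. The plan's own figures.**

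- Implied mean: 18/0.10 = 27/0.15 = 180 min per day. Standardised effect: 27/25 = 1.08, as stated.
- The generalised least squares covariance of the four fixed effects gives SE(γ20) between 3.86 and 5.38 min.
- Power = Φ(δ/SE − 1.96).
- For 18 min: Φ(18/5.38 − 1.96) = Φ(1.39) = 92% at worst, and Φ(18/3.86 − 1.96) = Φ(2.70) = 99.7% at best.
- For 27 min: Φ(27/5.38 − 1.96) = Φ(3.06) = 99.9% at worst.

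The stated powers (above 80% and above 99%) hold as lower bounds for γ20 tested alone.

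**3. Error of the either-suffices reading.**

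With no effect, the two z-statistics are bivariate normal with the model's own correlation ρ, so

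family-wise error = 1 − P(|Z₁| < 1.96 and |Z₂| < 1.96; ρ).

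| Stay | SDs (Day, Phase, Day_post) | ρ | Error |
|---|---|---|---|
| log-normal | 0, 0, 0 | 0.748 | 8.1% |
| fixed 24 | 0, 0, 0 | 0.663 | 8.5% |
| fixed 24 | 2, 20, 2 | 0.527 | 9.0% |
| fixed 21 | 3, 25, 3 | 0.445 | 9.2% |

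For reference, independent tests would give 1 − 0.95² = 9.75%, and the upper bound is 0.05 + 0.05 = 10%.

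Simulation of 4,000 null trials in each of two log-normal settings gave 7.9% (SDs 0, 0, 0) and 9.3% (SDs 2, 20, 2), against 8.1% and 9.0% from the formula. The Monte Carlo standard error is about √(0.09 × 0.91/4000) = 0.45 percentage points.

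**4. Other readings and repairs.**

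- γ20 alone at 0.05: 5% error, with the power in step 2.
- One joint test of γ20 = γ30 = 0: simulated error 5.2% and 4.9% in the same two settings.
- 0.025 for each coefficient: family-wise error 4.2–4.7%, with power for an 18 min level change of 86–99%.

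**5. How weak the second route is.**

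SE(γ30) is 1.03 to 1.25 min per day, so the slope change detectable with 80% power is (1.96 + 0.84) × SE, about 2.9 to 3.5 min per day. This agrees with the plan's remark that only larger slope effects are within reach.

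**The case against.** The strongest reply has three parts.

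First, the article never says that each coefficient is tested at 0.05. The 0.05 appears only with the power for γ20, and the hypothesis test is referred to in the singular, which also fits one joint test that would hold 5%. This stands. A reader might infer that the 5% error rate is simply not held, but the text supports only a conditional statement. It does not remove the contradiction, because a joint test would still make γ30 part of the confirmatory analysis.

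Second, an analysis plan that is not shown may contain an alpha split or a hierarchy. That is fair, so the absence of a multiplicity rule is not the point here. But no separate plan can make two published statements about γ30 agree.

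Third, the sample-size section already shows the intended order, with γ20 primary and γ30 exploratory. That is probably so, and it is why the repair is small. The test is nevertheless defined in the analysis section, which says otherwise.

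Two further inferences are tempting and not supported. One is that a significant fall in slope would count as success. A two-sided test against zero is ordinary practice, the Objectives speak of increasing activity, and the Study design section speaks of improvements, so the direction of interest is already fixed. The other is that levelling-off recovery would make one or other coefficient significant in almost every null trial. The article gives no recovery curve from which to calculate this. It would also be a matter of model misspecification, which no multiplicity rule cures.

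**Conclusion.** The plan is wrong as written on one definite matter: γ30 is inside the primary hypothesis test in one section and exploratory in another. The consequence for the error rate is conditional. It is about 8–9% instead of 5% if the rule means two separate tests at 0.05 with either sufficient, and 5% if it means a joint test.

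The 8–9% rests on the plan's variance inputs, the assumed random-effect SDs, a correctly specified model and known variance components; estimating those components could shift it slightly. Over the assumed range it moves only from 8.1% to 9.2%, so the conclusion does not depend on any particular choice.

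**What to change.** In the Quantitative analysis section, delete and/or. State that the primary hypothesis test is γ20 = 0 at two-sided alpha 0.05, and that γ30 is exploratory and reported with a 95% confidence interval. This follows what the Sample size justification already says and needs no change to the design, the sample size or the stated power. It should be settled before Phase 3 begins, which the article anticipates from end 2026.

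The only cost is the loss of the second route to a positive primary result. If the sponsor wants γ30 to remain confirmatory, the alternative is to name a joint test or 0.025 for each coefficient, and to withdraw the exploratory label for γ30 in the sample-size section.

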If improvements in activity consistently emerge following dashboard activation, despite activation occurring at five different timepoints across participants, this provides strong evidence that the dashboard, rather than natural recovery or external factors, is responsible for the observed changes (28). The design effectively controls for maturation (natural recovery trajectory would not systematically align with randomly varied onset points), history (external events affect all patients regardless of onset assignment), and regression to the mean (pre-intervention trends are explicitly modelled). This logic of experimental control is identical to that of the concurrent MBD across participants: the demonstration of the experimental effect is replicated each time a new participant transitions from A to B at a different time point, while other participants remain in baseline (27, 31). With 50 participants across five strata, the study provides 50 such demonstrations, far exceeding the minimum of three required by SCED standards (27). A schematic of the design, showing the baseline phase, the staggered randomized A → B onset across the five strata, and the continuous outcome-measurement timeline, is provided in Figure 1.

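### Phase and Day_post are defined by dashboard activation, yet all analyses are tied to the assigned onset day; weekend deferral separates the two for about 2/7 of patients

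*Protocol article*

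**What the plan says.** Study design (Phase 3) assigns each patient "to one of five onset points: post-admission day 3, 4, 5, 6, or 7", and adds: "If the assigned onset day falls on a weekend, activation will be deferred to the next weekday". The assigned day and the activation day are therefore two different quantities. The same section gives a baseline of 3 to 7 days with a 72-hour minimum.

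Quantitative analysis describes the target as the within-person effect of activating the dashboard. Phase is 1 once the dashboard is on, and Day_post is "0 during baseline, days since activation during intervention". The section ends its list of sensitivity analyses with "All analyses will follow the intention-to-treat principle based on assigned onset day".

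Sample size justification names the immediate level change, γ₂₀, as the parameter for which the study is primarily powered.

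**The concern.** For a patient whose assigned day is a Saturday or Sunday, the variable definitions and the intention-to-treat sentence put the phase change on different days. No sentence says that the assigned day means the day after deferral. Sensitivity analyses (a) to (e) do not settle it: the one-day lag in (b) shifts every patient, whereas deferral affects only some, and by one or two days.

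This is not a detail left for an analysis plan, because the article fixes both rules in one section and they disagree. Two analysts following the text could report different primary estimates, and a choice made after seeing the data would be an avoidable freedom. If the assigned-day sentence is taken literally, untreated days directly after the nominal onset enter the model as treated and pull γ₂₀ down.

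**Working it through.** **Inputs from the article.** Onset days 3–7 with 10 patients each; weekend deferral; residual SD 25 min, intercept SD 40 min, autocorrelation 0.3; a median of 24 daily observations; effects of 18 and 27 min; two-sided α = 0.05. **Assumed.** Admission weekday pattern; 24 days for every patient; SDs of the random effects for Day, Phase and Day_post, which the article does not give, set at (0, 0, 0), (1, 10, 1) and (2, 15, 2).

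**1. The plan's own figures.** 27/25 = 1.08, as stated. For the piecewise model with no deferral, the generalised least squares (GLS) standard error of γ₂₀ is 3.95 to 4.53 min across the three settings. Power ≈ Φ(effect/SE − 1.96):
- 18/3.95 = 4.56 gives 99.5%, and 18/4.53 = 3.97 gives 97.8%.
- 27 min gives above 99.9%.

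Both stated lower bounds (over 80% and over 99%) are met.

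**2. How often the two days differ.** Admission is counted as day 0, which the 72-hour minimum implies. Activation day for assigned days 3, 4, 5, 6, 7:

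| Admitted | 3 | 4 | 5 | 6 | 7 |
|---|---|---|---|---|---|
| Mon | 3 | 4 | 7 | 7 | 7 |
| Tue | 3 | 6 | 6 | 6 | 7 |
| Wed | 5 | 5 | 5 | 6 | 7 |
| Thu | 4 | 4 | 5 | 6 | 7 |
| Fri | 3 | 4 | 5 | 6 | 7 |
| Sat | 3 | 4 | 5 | 6 | 9 |
| Sun | 3 | 4 | 5 | 8 | 8 |

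The days differ in 10 of 35 cells, 28.6% (2/7), by 15/10 = 1.5 days on average. Monday–Friday admissions give 7/25 = 28.0%; Monday–Saturday, 8/30 = 26.7%. With admission as day 1 the three shares are 28.6%, 36.0% and 30.0%. Of 50 patients, that is about 14 (13 to 18).

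**3. Size if the assigned day governs.** Let μ hold a true 18-min jump at activation and let X be coded from the assigned day. The expected estimate is (ΣX′V⁻¹X)⁻¹ ΣX′V⁻¹μ. With uniform admissions and random effects tied to true activation:

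| Random-effect SDs | Expected γ₂₀ | Loss | Power, assigned-day coding | Power, activation coding |
|---|---|---|---|---|
| (0, 0, 0) | 15.3 | 15% | 97.2% | 99.7% |
| (1, 10, 1) | 14.6 | 19% | 94.0% | 99.2% |
| (2, 15, 2) | 13.9 | 23% | 88.6% | 98.3% |

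If the random effects are also coded from the assigned day, the estimate is 15.3 min in all three settings, with power 92–97%. Activation coding returns 18.0 min throughout. With no true effect, and no weekday pattern in activity, both codings return zero.

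**4. Why activation coding is not safe alone.** Activation never falls on a weekend. With uniform admissions, assigned Saturdays, Sundays and Mondays all activate on Monday, so 3/7 of activations directly follow a weekend. Study setting says therapy runs five days a week, so a weekday pattern in activity is plausible; its size is not given. Under no true effect (uniform admissions, random intercept only):

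| Assumed weekend deficit | Deferred-day coding, no weekend term | Assigned-day coding |
|---|---|---|
| 10 min | +3.3 | 0 |
| 20 min | +6.5 | 0 |
| 30 min | +9.8 | 0 |

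With Monday–Friday admissions the bias per 10 min is about +4.8 for deferred-day coding and +1.7 for assigned-day coding. A weekend indicator removes the bias and restores 18.0 min for a true 18; in the uniform, random-intercept case the standard error moves only from 3.82 to 3.86.

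**The case against.** The strongest reply is that nothing is diluted if the model is fitted as its variables are defined: Phase and Day_post both follow activation. The intention-to-treat sentence could mean only that patients are kept as randomised, or it could mean the assigned day after the weekend rule. That stands to this extent: the text shows an unresolved conflict, not a demonstrated dilution. A reader might infer that the primary effect is certain to be underestimated. The documents do not support that, because the loss arises only under one of the two rules.

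It is also true that the adverse reading is conservative and leaves the stated power bound intact.

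Two further inferences are tempting. One is that deferral collapses the stagger, since Monday, Tuesday and Wednesday admissions each have only three distinct activation days. But the design's contrast is across participants ("despite activation occurring at five different timepoints across participants"). Pooled over the 35 cells, activation on days 3 to 9 occurs 5, 6, 7, 7, 7, 2 and 1 times, so days 3–7 remain well filled. The other is that the miscoded days alone identify γ₂₀. The whole series before and after onset informs it, and the calculated loss of 15–23% is below the roughly 28% expected if those days carried all the information.

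**Conclusion.** The conflict is real and rests on the article's own wording. It affects about 2/7 of patients, or 27–36% over the admission patterns and day numberings tried; the article gives no admission-weekday distribution. If the assigned-day sentence governs, γ₂₀ loses roughly 15–23% (18 min becomes about 14–15). That range depends on assumed random-effect SDs and a common 24-day stay. Dilution lowers power but does not by itself inflate type I error, and power stays above 80% in every setting tried.

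A smaller inconsistency goes with it. With admission as day 0, a weekend admission can be activated on day 8 or 9, beyond the stated 3-to-7-day baseline. Whether weekend admissions occur is not stated.

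**What to change.** - In the primary model, define Phase and Day_post from the scheduled activation day: the randomised day after the fixed weekend rule, whether or not activation took place. That day is determined by the allocation and the admission weekday, both known at randomisation, so intention-to-treat is preserved. Reword the closing sentence of Quantitative analysis to say so.
- In the same change, add a weekend or day-of-week term to the primary model. The first step should not be adopted without it, because it would replace a bias toward the null with a possible false positive.
- Keep assigned-day coding as a named sensitivity analysis.
- Reconcile the stated baseline length with the deferral rule in Study design.

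The cost is one definition, one extra model term and a negligible rise in the standard error. No patient, visit or measurement changes, and the article reports the study as still in Phase 1, before the randomised evaluation.
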